### Experiment setup

3.4

Our predictive models were constructed using Python 3.7.13, leveraging libraries such as Pandas for data manipulation, scikit-learn for machine learning algorithms, and NumPy for numerical computations.

## Randomized controlled trial

4

### RCT design and methods

4.1

Our study employs a parallel-group RCT to evaluate the effectiveness of an AI-based exercise prescription system in mental health management. Participants are divided into two groups: an intervention group and a control group, each consisting of 25 individuals. This balanced design allows for a robust comparison of outcomes between the groups, thereby providing reliable evidence on the impact of the AI-driven intervention. The randomization process involves a computer-generated sequence, ensuring an unbiased assignment of participants into the intervention group (*n* = 25) and the control group (*n* = 25). Stratification is conducted based on key variables such as age, gender, and specific mental health diagnoses to maintain comparable groups. This methodology is critical for mitigating potential confounding factors and ensuring the validity of the study results. In the intervention group, each participant receives a personalized exercise prescription tailored by the AI system, based on their unique health profile. This approach aims to maximize the efficacy of the exercise regimen in improving mental health outcomes. The control group, on the other hand, receives standard care practices, which may include general health advice or standard exercise recommendations. The distinction in treatment between the groups is central to evaluating the added value of the AI-driven exercise prescriptions.

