**Methods:**

The study is conducted in two phases. Initially, 1,000 participants will be recruited for AI model training and testing, with 800 forming the training set, augmented by 9,200 simulated samples generated by ChatGPT, and 200 as the testing set. Data annotation will be performed by experienced physicians from the Department of Mental Health at Guangdong Second Provincial General Hospital. Subsequently, a randomized controlled trial (RCT) with 40 participants will be conducted to compare the AI-driven exercise prescriptions against standard care. Assessments will be scheduled at 6, 12, and 18 months to evaluate cognitive, physical, and psychological outcomes.

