### Study design

2.1

In the first phase, we focus on developing a multimodal data-driven intelligent system for exercise prescription. To achieve this, we will initially recruit 1,000 participants for AI model training and testing. Of these, 80% (800 participants) form the training set. To enhance the robustness and generalizability of the AI model, we will use ChatGPT to simulate an additional 9,200 cases based on the initial 800, resulting in a comprehensive training set of 10,000 instances. The remaining 20% (200 participants) will be reserved as a testing set. This diverse dataset will then be annotated by a team of 10 experienced doctors from the Department of Mental Health at Guangdong Second Provincial General Hospital. Their expertise will ensures the accuracy and clinical relevance of the data labeling, which is critical for the development of a reliable and effective AI system.

In our analysis, we will set the effect size at 0.5 to assess the intervention’s effectiveness. This value represents a medium effect size, which is considered substantial in the context of our study. Following the development and preliminary testing of the AI model, the second phase of the study will involves an RCT with 50 participants. These participants are randomly divided into two groups: 25 in the experimental group and 25 in the control group. The experimental group will receives personalized exercise prescriptions generated by the newly developed AI system, while the control group will receives standard exercise recommendations. This phase aims to evaluate the efficacy of the AI-driven exercise prescription system in a real-world clinical setting. The RCT’s design ensures that the results are robust and can be attributed specifically to the intervention, thereby providing strong evidence of the system’s potential benefits for individuals with mental illnesses.

The effectiveness of the AI-driven exercise prescriptions is evaluated at multiple time points: initially at the end of the 6 months trial period (Trial Completion Assessment), followed by a 6 months follow-up assessment and a 12 months follow-up assessment. These assessments are designed to track and compare the short-term and long-term impacts of the AI-driven exercise prescriptions on the mental health outcomes of the participants (shown in Figure 1).

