### Inclusion criteria

2.4

In this study, participants are selected based on specific inclusion criteria to ensure both relevance and safety. Individuals aged 18 to 65, diagnosed with a mental illness such as depression, anxiety disorders, bipolar disorder, or schizophrenia, are eligible. They must be in a stable medical condition, with no acute mental health crises in the past 6 months, and have the cognitive ability to understand and consent to the study procedures. Physical capability for exercise, assessed by the PAR-Q Plus, is required, alongside a willingness to adhere to the study’s protocol. Participants should not be engaged in any other structured exercise program, have access to communication tools for remote monitoring, and reside within a distance from the study site in the Guangzhou area. These criteria are designed to ensure that participants are representative of the target population and can safely and effectively engage in the study.

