### Statistical analysis

4.5

In the initial phase of our statistical analysis, we will employ descriptive statistics to summarize the participant characteristics, including demographics, baseline health measures, and other relevant variables. This step will involve calculating means, standard deviations, and proportions to provide a clear overview of the study population. Following this, comparative analyses between the intervention and control groups will be conducted using independent *t*-tests (or Mann–Whitney U tests for non-normally distributed data) for continuous variables, and Chi-square tests (or Fisher’s exact tests) for categorical variables. This will enable us to detect any significant differences arising from the intervention.

Considering the multiple assessment points in our study, longitudinal data analysis techniques will be crucial. These methods, including repeated measures ANOVA or mixed-model ANOVAs, will allow us to track and analyze changes over time both within and between participant groups. This approach is essential for understanding the dynamics of the intervention’s impact, accounting for both individual variations and time-dependent factors.

To quantify the intervention’s effectiveness, we will calculate effect sizes, providing a measure of the practical significance of our findings. The handling of missing data, a common challenge in longitudinal studies, will be addressed through methods like multiple imputation or last observation carried forward, ensuring the robustness of our results. All statistical tests will be two-tailed, with a significance level set at *p* < 0.05. We plan to use sophisticated statistical software such as SPSS or R for these analyses, enabling us to apply the most appropriate and advanced statistical techniques for our data.

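### Randomisation is stratified by age, gender and diagnosis, but the stated between-group tests leave these factors out, which makes them conservative and costs power if the factors are prognostic

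*Protocol article*

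**What the plan says.** All references are to the protocol article.

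- **Section 4.1 (RCT design and methods), allocation.** The trial has two parallel arms, "each consisting of 25 individuals". On the method: "The randomization process involves a computer-generated sequence, ensuring an unbiased assignment of participants". On the factors: "Stratification is conducted based on key variables such as age, gender, and specific mental health diagnoses to maintain comparable groups". The section gives no age cut-points, diagnosis grouping or block size.
- **Section 2.4 (Inclusion criteria).** "Individuals aged 18 to 65, diagnosed with a mental illness such as depression, anxiety disorders, bipolar disorder, or schizophrenia, are eligible". The list of diagnoses is open.
- **Section 2.1 (Study design).** "the second phase of the study will involves an RCT with 50 participants", with an effect size of 0.5. The abstract gives a different total: "a randomized controlled trial (RCT) with 40 participants will be conducted". That conflict is a separate point; the body figure of 50 is used here.
- **Section 4.5 (Statistical analysis).** "comparative analyses between the intervention and control groups will be conducted using independent" t-tests, with Mann–Whitney as the fallback, and chi-square or Fisher tests for categorical variables. Repeated-measures or mixed-model ANOVAs follow for change over time. Tests are two-sided at 0.05. No stratification factor or other covariate is named for any of them.

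**The concern.** Factors are worth stratifying on when they are expected to predict outcome. Section 4.1 chooses three for that reason and presents the stratification as protection against confounding. Section 4.5 then uses two-sample tests with no place for those factors.

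The two choices fit badly together. Stratified allocation makes the arms more alike on the factors than chance would, so the true sampling variation of the treatment difference shrinks. The unadjusted test does not register this: the factor-related variance stays in its error term. The result is a test that rejects less often than 5% under the null, confidence intervals wider than needed, and lost power. In a trial of 50 whose power is already low at its own effect size, that is a loss worth avoiding.

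A secondary matter is the number of factors. Three crossed factors in 50 people can make very small cells, which bears on whether exactly 25 per arm can be promised.

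**Working it through.** **Inputs from the article:** 25 per arm; effect size 0.5 (outcome SD taken as 1); two-sided 0.05; factors age, gender and diagnosis; four named diagnoses.

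**Assumed, because the article does not state them:** two age bands, two genders and four separate diagnoses, all equally common and fully crossed; permuted blocks of 4 within cells; the three factors together explaining 20% or 40% of outcome variance, in equal shares.

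**1. Baseline power.** The article states no power, so there is no figure to reproduce. The standard error is √(2/25) = 0.283 and 0.5/0.283 = 1.77, so power ≈ Φ(1.77 − 1.96) = 0.42 (0.41 with the t distribution).

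**2. Direction of the effect.** Let the factors explain a share R² of variance.

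- With perfect balance, the true standard error is 0.283 × √(1 − R²), but the unadjusted test still uses about 0.283. Its type I error would be 2 × [1 − Φ(1.96/√(1 − R²))].
- R² = 0.2: √0.8 = 0.894, 1.96/0.894 = 2.19, type I error 0.028.
- R² = 0.4: √0.6 = 0.775, 1.96/0.775 = 2.53, type I error 0.011.

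Real balance is imperfect, so the actual values lie between these and 0.05.

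An adjusted analysis sees an effect of 0.5/√(1 − R²), which is 0.559 or 0.645. Power is then about Φ(0.559/0.283 − 1.96) = 0.51 or Φ(0.645/0.283 − 1.96) = 0.63. These are upper figures, before the cost of degrees of freedom and residual imbalance.

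**3. Simulation** (16 cells, blocks of 4, 6,000 trials per setting; the adjusted model has main effects of age band, gender and diagnosis).

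| Variance explained | Type I, unadjusted | Type I, adjusted | Power at 0.5, unadjusted | Power at 0.5, adjusted |
|---|---|---|---|---|
| 0% | 0.052 | 0.053 | 0.42 | 0.40 |
| 20% | 0.035 | 0.052 | 0.40 | 0.47 |
| 40% | 0.019 | 0.048 | 0.40 | 0.60 |

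A repeat of the 20% and 40% rows with 10,000 trials per setting gave 0.035 and 0.022 for unadjusted type I error, 0.39 for unadjusted power in both rows, and 0.47 and 0.60 for adjusted power. The results sit inside the limits of step 2.

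**4. Cell size (conditional).** 2 × 2 × 4 = 16 cells and 50/16 = 3.1 people per cell. Three age bands give 24 cells of 50/24 = 2.1. Two diagnosis groups give 8 cells of 50/8 = 6.3.

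**5. Arm sizes, N = 50.**

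| Scheme | Exactly 25:25 | 28:22 or worse | SD of difference |
|---|---|---|---|
| 16 cells, blocks of 2 | 27% | 7% | 2.9 |
| 16 cells, blocks of 4 | 21–22% | 17% | 3.7 |
| 16 cells, blocks of 6 | 17% | 27% | 4.6 |
| Simple randomisation | 11% | 48% | 7.1 |
| Diagnosis only, blocks of 4 | 42% | 0.3% | 1.8 |
| Minimisation, biased coin 0.8 | 61% | 0.1% | 1.4 |

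**6. Balance on the factors** (mean absolute difference between arms per level).

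| Scheme | Age | Gender | Diagnosis |
|---|---|---|---|
| 16 cells, blocks of 4 | 2.1 | 2.1 | 1.5 |
| Simple randomisation | 4.0 | 4.0 | 2.8 |
| Minimisation | 1.3 | 1.2 | 1.4 |
| Diagnosis only | 2.9 | 2.9 | 0.7 |

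**7. Cost of unequal arms.** At 29:21, 1/29 + 1/21 = 0.0821 against 2/25 = 0.0800, a 2.6% rise in variance.

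**The case against.** **The article is condensed.** Block sizes, stratum definitions and covariate lists commonly sit in a full protocol or SAP, neither of which is shown. For block sizes and stratum definitions this stands, and their absence is not held against the plan. For the ANOVA models it stands in part, since covariates could be added there. It does not cover the two-sample tests: a t-test or a Mann–Whitney test takes no covariates, and these are the methods the article states for comparing the arms.

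**The loss depends on unknown prognostic strength.** This stands. The article gives no figure. With no prognostic value, adjusting gains nothing and costs about 0.01 in power. The 20% and 40% cases show a range and are not estimates.

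**Over-stratification is not shown to do harm.** A reader might infer that cells of three cancel the benefit of stratifying and leave something near simple randomisation. Steps 5 and 6 contradict that: with blocks of 4, imbalance is about half that of simple randomisation, because even an unfilled block constrains allocation. Missing exactly 25:25 matters little for precision (step 7). The 16 cells are themselves a construction, as the four diagnoses come from the eligibility text and no levels are given for stratification. Choosing minimisation over stratified blocks is a legitimate design preference, and the plan is not wrong for lacking it.

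**Conclusion.** The point holds in a limited form. The article stratifies on three factors and states between-group tests that leave them out. If the factors explain 20% / 40% of outcome variance, the nominal 5% test runs at about 0.04 / 0.02, and power at an effect of 0.5 with 25 per arm stays near 0.40 when adjustment would give about 0.47 / 0.60. These figures rest on the cell structure, blocks of 4 and equal factor contributions assumed above.

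A reader might infer that a chance imbalance in diagnosis could produce a false positive result. The calculation points the other way: under this stratification the unadjusted test is conservative. Its cost is lost power and wide intervals, not a raised false positive rate.

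The secondary point is conditional. If the factors are fully crossed with at least two age bands and four diagnoses, cells hold about three people and exactly 25:25 occurs in about 21% of trials with blocks of 4. Arm sizes and factor balance would still be better than under simple randomisation. Minimisation would do better on both; fewer strata would hold arm sizes closer but give up balance on any factor dropped. The article presents 25 per arm as fixed, which blocked strata of that kind cannot guarantee.

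**What to change.** - **Section 4.5.** Replace the two-sample comparison of continuous outcomes with a linear model, or a mixed model for repeated assessments, that includes arm, diagnosis, gender and age as a continuous covariate. With four diagnoses this uses five degrees of freedom (three for diagnosis, one each for gender and age). The unadjusted tests can remain as supporting results.
- **Section 4.1.** Describe 25 per arm as a target, unless the allocation scheme forces it. State the levels of each stratification factor so that they match the terms in the model.
- **Optional.** If the factors are to be fully crossed, consider stratifying on fewer of them or using minimisation with a random element. This means a different allocation routine and must be settled before the first randomisation. The model change does not depend on it.

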### Intervention measures

4.2

The 25 participants in the intervention group receive personalized exercise prescriptions generated by our AI model. These prescriptions are meticulously tailored based on each participant’s health profile and mental health status. The AI model determines the most suitable Type of Exercise for each individual, ranging from aerobic activities to strength training, depending on their physical and mental health needs. The Frequency of exercise is set, aiming for a balance that maximizes benefit while considering each individual’s lifestyle and capacity. Intensity levels are also customized, ensuring that exercises are challenging yet safe and achievable for each participant. Lastly, the Duration of each exercise session is specified by the AI model, optimizing the time spent on each activity for maximum efficacy. For example, for a participant with moderate depression and a sedentary lifestyle, the AI model might prescribe light aerobic activities like brisk walking or cycling for 30 min, three times a week. The intensity would be set at a moderate level, ensuring the participant can comfortably sustain the activity while gaining mental health benefits. The model may also suggest gentle yoga twice a week to improve flexibility and reduce stress, tailoring the duration to 20 min per session to match the participant’s initial physical fitness level. The intervention lasts for a period of 4 weeks, during which participants adhere to their personalized exercise regimen. The control group, comprising another set of 25 participants, receives standard care practices. This generally includes generic health advice and non-tailored exercise recommendations, reflecting the conventional approach to mental health management. The control group’s treatment does not involve the AI-driven customization of exercise parameters, serving as a baseline to evaluate the effectiveness of the personalized exercise prescriptions provided to the intervention group.

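### The only stated intervention length is 4 weeks, yet the first listed outcome visit is month 6, labelled trial completion, and nothing reconciles the two

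*Protocol article*

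**What the plan says.** Section 4.2 (Intervention measures) fixes the treatment: "The intervention lasts for a period of 4 weeks, during which participants adhere to their personalized exercise regimen". This is the only intervention length in the document.

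Section 2.1 (Study design) evaluates effectiveness "initially at the end of the 6 months trial period (Trial Completion Assessment"). The same sentence then sets out two later visits: "followed by a 6 months follow-up assessment and a 12 months follow-up assessment". Section 2.1 gives the purpose as follows: "These assessments are designed to track and compare the short-term and long-term impacts of the AI-driven exercise prescriptions".

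Section 4.3 and Table 2 use the same schedule: month 6 as trial completion, month 12 as first follow-up, month 18 as second follow-up. The abstract gives the same months without the trial-completion label: "Assessments will be scheduled at 6, 12, and 18 months to evaluate cognitive, physical, and psychological outcomes".

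Table 2 has no baseline column and no week-4 column. Section 4.5 does plan to summarise baseline health measures, so a baseline measurement is implied. Figure 1, which section 2.1 cites for the design, is not shown in the text available.

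Section 2.3 (Time frame) describes a two-year follow-up after trial completion.

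**The concern.** The visit labels and the intervention length point in different directions. Calling month 6 completion and month 12 the first follow-up suggests that treatment runs to month 6. Section 4.2 says it ends at week 4. Whether participants are meant to keep exercising after week 4 is not stated.

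The two readings describe different treatments, with different consequences:

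- **Six months is meant.** Then 4.2 is wrong, and staff who follow it will stop the regimen early. No analysis can repair that afterwards.
- **Four weeks is meant.** The randomised comparison at month 6 is still valid, but it estimates what persists months after the regimen. No visit listed in the text measures the effect when the regimen ends, although 2.1 says short-term impact is tracked. A null result at month 6 would then be ambiguous.

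**Working it through.** The article reports no figure here to reproduce. The check sets the stated times side by side and counts.

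**Inputs**

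| Item | Value | Source |
|---|---|---|
| Intervention length | 4 weeks | 4.2 |
| First listed outcome visit | month 6, trial completion | 2.1, 4.3, Table 2 (abstract: month only) |
| Later visits | months 12 and 18 | 4.3, Table 2, abstract |
| Illustrative regimen | 30 min aerobic three times a week, plus 20 min yoga twice a week | 4.2 |
| Follow-up after completion | two years | 2.3 |
| Trial size | 50 (2.1, 4.1) or 40 (abstract) | as shown |

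Six months is taken as 26 weeks.

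**Gap from the end of a 4-week regimen to the first listed outcome.** The time origin is not stated, so each line is an assumption.

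- Months counted from regimen start: 26 − 4 = 22 weeks.
- Months counted from regimen end: 26 weeks.
- Months counted from a randomisation *d* weeks before the start: 22 − *d*. With *d* = 4, chosen only for illustration, this is 18 weeks.

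On the start-based clock the regimen fills 4/26 = 15% of the 6-month period. Months 12 and 18 fall 52 − 4 = 48 and 78 − 4 = 74 weeks after it ends. If the regimen instead runs the full 6 months from that origin, the gap at month 6 is 26 − 26 = 0.

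**Early stop if 6 months is meant:** 26 − 4 = 22 weeks.

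**Dose under each reading.** The example in 4.2 starts from "light aerobic activities like brisk walking or cycling for 30 min, three times a week" and adds the yoga sessions.

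- Per week: 3 + 2 = 5 sessions; 3 × 30 + 2 × 20 = 130 min.
- Over 4 weeks: 5 × 4 = 20 sessions; 130 × 4 = 520 min.
- Over 26 weeks: 5 × 26 = 130 sessions; 130 × 26 = 3,380 min.
- Ratio: 3,380/520 = 26/4 = 6.5.

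The ratio holds for any constant weekly regimen and does not depend on the time origin.

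**Separate minor check on 2.3.** The schedule ends 18 − 6 = 12 months after completion. Section 2.3 states 24.

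**The case against.** The strongest reply is that nothing is strictly contradicted. Section 4.2 gives the length of the intervention and 2.1 the length of the trial period, and a 4-week regimen can sit inside a 6-month trial. No sentence says the regimen runs for 6 months. On that literal reading the month-6 comparison is sound, and an end-of-regimen visit is a design preference. Short-term in 2.1 may simply mean month 6 as against month 18. Figure 1 is not visible, and a journal article may leave the time origin and post-regimen instructions to the full protocol.

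Much of this is fair. The nested reading is possible, and the claim is that no earlier outcome visit is listed in the text, not that none exists. The session and minute totals come from one hypothetical participant, so the 6.5 ratio is the real content. The 18-week figure rests on an assumed delay. At week 4 the PSQI's recall would cover the regimen as a whole and not just its last days, and two questionnaires would not cover the cognitive and physical outcomes.

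The core remains. The article did not omit the intervention length in condensing: it states both durations and leaves them unreconciled. The nested reading also fits the visit labels poorly, because month 6 would itself be follow-up to a regimen that ended months before.

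**Conclusion.** The concern holds and should be fixed before the trial is run. The intervention length in 4.2 and the trial-completion visit at month 6 are not reconciled anywhere in the text, and the two readings differ 6.5-fold in planned exercise.

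If 6 months is intended, following 4.2 ends treatment about 22 weeks early. If 4 weeks is intended, the first outcome listed in the text comes about 22 weeks after the regimen when months run from its start, or 26 when they run from its end (18 under the illustrative pre-start randomisation). Either way an action is needed.

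These sizes assume 26 weeks in 6 months and the time origins named. The absence of an earlier visit is judged from the text alone. The two-year follow-up in 2.3 is a separate, minor error and does not drive this conclusion.

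**What to change.** State one intervention length and the time origin of the visits, identically in 2.1, 4.2, 4.3 and Table 2. Which length is a clinical decision for the sponsor.

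- **If 6 months:** correct the sentence in 4.2. Month 6 is then the end-of-intervention visit. The cost is wording only.
- **If 4 weeks:** give the STAI and PSQI remotely to both groups at week 4, and label month 6 as post-intervention follow-up. Both instruments are already scheduled (STAI at months 6 and 18; PSQI at 6, 12 and 18), so the week-4 values have later ones to compare with. The PSQI's previous-month recall (Table 1) spans the 4-week regimen. Also say whether participants are asked to continue exercising after week 4.

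The extra visit costs one remote contact per participant. That is 50 × 1 = 50 contacts under 2.1 ("the second phase of the study will involves an RCT with 50 participants") or 40 × 1 = 40 under the abstract ("a randomized controlled trial (RCT) with 40 participants will be conducted"). Section 2.4 already requires participants to have the means for remote monitoring.

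As a separate minor correction, change the two-year follow-up in 2.3 to 12 months after trial completion (month 18), in line with the schedule.
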